### Plans to give access to the full protocol, participant-level data, and statistical code {31c}

Once the project is finished, all data (excluding personal, identifying data) and statistical code will be uploaded to ISRCTN registry, a registry specifically for clinical research.

### Composition of the data monitoring committee and its role and reporting structure {21a}

Given the minimal risk of this intervention and its brief duration, an independent Data Monitoring Committee is unnecessary. Participant safety during the intervention will be the responsibility of attending researchers and coaching staff. Any adverse events will be reported to the principal investigator and documented (see item {22}).

### Adverse event reporting and harms {22}

Potential adverse events and harms include the following: slips, trips, and falls, immersion in water, water-borne diseases/infection, thunder and lightning, exposure to animal waste, psychological distress/PTSD flashbacks, etc. Mitigations for such adverse effects include the following: pre-event inspection of lakeside, initial safety talk to participants, observation by coaches, provision of hand-washing facilities and hand sanitising gel, and a mental health professional will attend to observe and monitor any signs of distress. The mental health professional’s role will be to administer mental health “first aid” to any participants whose PTSD symptoms might be triggered during the intervention. First aid will include grounding techniques, emotional regulation procedures, and psychoeducation around the symptoms they may be experiencing.

Serious adverse events (SAE, untoward occurrences that result in harm) are reported by the PI to the sponsor within 24 h of becoming aware of the event. The sponsor reviews all reports within 2 days of receiving the report, and the outcome is recorded in the site management file and the sponsors’ research governance committee. SAEs that are determined to be related and unexpected are reported to the ethics committee.

#### Nonserious adverse events

Written records are made by those running the intervention in the Health Incident Report form and reported to the PI. These forms are reviewed by PI and checked to see if further action is required.

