### Interim analyses {21b}

The intervention is brief, consisting of a 2-day/1-night weekend, and follow-up surveys occur within 4 weeks. The trial is subject to a power analysis for a final sample size of 196 with no early stopping and no interim analyses. The intervention is minimal risk due to the nondrug nature of the intervention. Injuries occurring on the intervention are reported, and this does not require an interim analysis.

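### Non-serious harms are described as recorded only by event staff, with no adverse event question in either arm's 2- and 4-week surveys, so delayed events are likely to be under-counted and rates cannot be compared between arms

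*Protocol article*

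**What the plan says.** All references are to the protocol article.

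- **Hazards.** Adverse event reporting and harms {22} lists "slips, trips, and falls, immersion in water, water-borne diseases/infection, thunder and lightning, exposure to animal waste, psychological distress/PTSD flashbacks, etc". For distress, "a mental health professional will attend to observe and monitor any signs of distress".
- **Non-serious events.** Under Nonserious adverse events: "Written records are made by those running the intervention in the Health Incident Report form and reported to the PI". The principal investigator (PI) then reviews the forms.
- **Serious events.** Item {22} defines them in these words: "Serious adverse events (SAE, untoward occurrences that result in harm". They "are reported by the PI to the sponsor within 24 h of becoming aware of the event".
- **Scope elsewhere.** Interim analyses {21b}: "Injuries occurring on the intervention are reported, and this does not require an interim analysis". The data monitoring committee section {21a}: "Participant safety during the intervention will be the responsibility of attending researchers and coaching staff". The next sentence there is general: "Any adverse events will be reported to the principal investigator and documented (see item {22".
- **Surveys.** Outcomes {12} lists the instruments and their timing. PCL-5, PHQ-9, GAD-7 and the wellbeing scale are taken in both arms 2 weeks before the intervention and 2 and 4 weeks after it. Loneliness, anger and work and social adjustment are secondary. No adverse event item is listed.
- **Responder analysis.** Outcomes {12} and Secondary analyses {20a} count falls in PCL-5 of at least 10 points (clinically significant change) and at least 5 points (reliable change).

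**The concern.** The hazards the article names and the way it says they will be caught do not match. A form completed by people at the lake can catch a fall or a flashback at the lake. It has no described way to catch an infection that shows a week later, or distress that builds after the participant goes home. In the randomised period the waitlist arm attends no event, so no such form can exist for it.

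Two things are at stake. First, a nearly empty table of non-serious harms could be read as evidence of safety when it partly reflects where the trial looked. Minimal or low risk is the article's reason for having no data monitoring committee, no interim analysis and no audit, and the described capture cannot test that premise well. Second, the Discussion says the results should inform policy and commissioning, and those readers will want harms set against a control.

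**Working it through.** No figure in the article bears on this point, so the check is a comparison of sections.

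**1. Who records, and when?** For non-serious events the only recorder described is the staff running the event. No later contact is described as asking about adverse events. The reminder procedure in {18b} concerns survey completion, and the health service use follow-up in Outcomes {12} comes at 6 and 12 months in the intervention group only.

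**2. Can the named hazards fall outside that route?** The event lasts 2 days and 1 night. I assume, as a general matter, that an infection acquired there need not show before departure and that distress can follow the return home. The article gives no onset times.

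**3. What of serious events?** That route starts when the PI becomes aware. It is not limited to the 2 days or to one arm, but no active ascertainment is described. The definition has no seriousness threshold: read literally, any occurrence that causes harm qualifies. It therefore overlaps with the separate non-serious category, and the same event could go down either route.

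**4. Can arms be compared?** The Intervention description {11a} says the waitlist group receives no intervention in the comparison period. No incident form can arise for it then, so the described route yields no control rate of non-serious events for the randomised period.

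**5. Do the symptom scales fill the gap?** In part. Mean PCL-5, PHQ-9 and GAD-7 changes can be compared between arms, so average worsening would show. A worsening minority need not. Suppose, for illustration, that a fraction w of an arm rises by the plan's own 10 points and the rest fall by 10:

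mean change = 10w − 10(1 − w) = −10(1 − 2w)

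This is an improvement for any w below one half. The planned responder proportion is then 1 − w, which does not separate those who worsened from those who did not change. The scales also say nothing about infection or injury.

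**6. Scale, as illustration only.** From arrival to the 4-week survey is about 2 + 28 = 30 days. If non-serious recording stops at departure (an assumption), it covers 2/30 = 6.7% of that window. This is a share of time, not of events missed. Likewise, a zero-event upper bound such as 1 − 0.05^(1/132) = 2.2% describes sample size, assumes all 132 active participants attend, and covers only harms visible on site. Neither figure measures an under-count.

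**The case against.** The strongest reply is that the quoted sentence concerns non-serious events only. Serious events have their own route, and item {21a} sends any adverse event to the PI, with no limit of time or arm. That stands. A reader might infer that all harms are recorded only by event staff, or that later harms can never be recorded. The documents do not support either. What they lack is a described step that would bring a later event to the PI's attention.

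A reader might also infer that no harm is recorded in the waitlist arm. That is partly an argument from silence. The statement in {11c} that waitlist activities are not monitored concerns adherence, nothing excludes these participants from the serious event route, and they attend the same event later, when the incident form applies to them. What stands is that the described non-serious route cannot produce data on them during the randomised comparison.

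Nor is it right that harms cannot be attributed, or that worsening cannot be separated from its background rate. Item {22} provides for a judgement of relatedness and expectedness for serious events, and the symptom scales are taken in both randomised arms.

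Finally, this is a condensed article. The full protocol may say more, and the timeline figures are not shown. That is a fair caution. But item {22} does state the recorder, the form and the review, and Outcomes {12} lists the survey instruments in detail. The criticism is of a stated route that is too narrow. If the full protocol has a wider one, most of the fix reduces to saying so.

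**Conclusion.** The concern holds for non-serious events. As described, events that appear after departure are likely to be under-counted, and non-serious event rates cannot be compared between arms in the randomised period. Average symptom worsening can be compared, but no planned analysis reports the proportion who worsen. The serious event definition and the non-serious category overlap and must be reconciled.

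The size of any under-count cannot be calculated, because the documents give no harm rates. The conclusion assumes that some named hazards can appear after the stay, and that the surveys carry no harms items beyond the instruments listed. It is a weakness in how harms are measured. It does not show that the intervention is unsafe, and it does not affect the primary comparison.

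**What to change.** **(a) Widen capture.** In Adverse event reporting and harms {22} and Nonserious adverse events, extend non-serious event capture to the 4-week survey. Add the same short, neutrally worded items to the existing 2- and 4-week surveys of both arms: illness or infection, injury, unplanned healthcare contact, worsening distress. Use them also in the waitlist group's surveys after its own session. Report by arm for the randomised period, and pooled over everyone exposed.

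**(b) Report deterioration.** Beside the responder analysis, report by arm the proportion whose PCL-5 rises by at least 5 and at least 10 points at 2 and at 4 weeks. This uses data already being collected and covers all participants who complete those surveys.

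**(c) Reconcile the categories.** Make the serious event definition and the non-serious category mutually exclusive, so that each event has one route.

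**Cost.** About a minute of extra survey time, more non-serious reports for the PI to read, and one or two tables. No extra staff are needed. Part (a) is an amendment and, under {25}, needs approval from the sponsors, the University Ethics Committee and the Health Research Authority. Recruitment began in March 2024 and is due to end in September 2026, so item data will exist only for participants surveyed after the change. The report must say so. Introducing the items in both arms at the same time keeps the comparison fair among those who receive them.

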### Frequency and plans for auditing trial conduct {23}

The intervention is brief, low risk, on a single site, and is a behavioural intervention, and as such, there are no plans for auditing trial conduct. The research team are responsible for monitoring all aspects of the ongoing procedures.

### Plans for communicating important protocol amendments to relevant parties (e.g. trial participants and ethical committees) {25}

Changes to the protocol require ethical approval from the sponsors, the internal University Ethics Committee, and the Health Research Authority.

### Dissemination plans {31a}

The primary outcome will be the analysis of change in PTSD symptoms pre- and post-intervention for intervention groups versus waitlist control groups. This will be disseminated in the following ways:Liaise with the Department of Health and Social Care (DHSC) to hold a workshop on NBIs for policymakers.Finalise intervention manual to ensure consistent intervention delivery going forwards.Create plain English information pamphlet to provide clear information about the intervention.A written report to the funderPapers submitted for publication in leading academic journalsPresentations at academic/health/environmental conferences and forumsDissemination events at the University of Essex and elsewhere to publicise the study findings, to distribute our plain English summary, and to develop further ties with service providers

## Discussion

This study aims to address the critical issue facing military veterans and emergency service personnel, namely the barriers to standard psychotherapeutic provisions by providing evidence for a nature-based alternative. Importantly, this trial will employ a large-scale adequately powered randomised controlled trial sensitive enough to detect clinically significant changes in PTSD symptoms. Beyond PTSD symptoms, this study will rigorously investigate comorbid symptoms of PTSD, potential mechanisms to recovery, and the cost-effectiveness of the intervention. No such large-scale study has previously investigated the efficacy of angling as a nature-based intervention to help reduce PTSD symptoms in military veterans and emergency service personnel.

Some practical issues involve recruitment and retention from target populations that are sometimes difficult to engage in research. For example, one barrier to entry is not recognising that symptoms are psychological [3], so that some people from this particular population will not engage in research addressing psychological illness. This difficulty in engagement also makes ensuring the completion of follow-up surveys difficult. Indeed, pilot data indicates attrition rates after randomisation as high as 25%. Recruitment targets have therefore been adjusted accordingly.

The findings will provide valuable causal evidence on the potential of nature-based interventions to support recovery from PTSD and inform future policy and commissioning of social prescribing initiatives.

### Trial status

The study is currently recruiting. Recruitment began in March 2024 and ends September 2026. Currently, we are attempting to expand the participant pool by including tube/train drivers and serving military personnel. However, that ethical approval process is ongoing. The current protocol is version 1 (01/03/2024).

## Data Availability

The datasets generated during and/or analysed during the current study are available from the corresponding author on reasonable request. Once the project is finished, all data (excluding personal, identifying data) and statistical code will be uploaded to ISRCTN registry.

## Abbreviations

Angling Trust: National Governing Body for Angling in England
CIC: Community interest company
DHSC: Department of Health and Social Care
ESNEFT: East Suffolk and North Essex NHS Foundation Trust
ESP: Emergency service personnel
EEPRU: Essex ESNEFT Psychological Research Unit for Behaviour, Health and Wellbeing
GAD-7: General Anxiety Disorder-7 scale
NHS: National Health Service
NBI: National Health Service
NIHR: National Institute for Health and Care Research
NICE: National Institute for Health and Care Excellence
PHQ-9: Patient Health Questionnaire-9
PRS: Perceived Restorativeness Scale
PRP: Policy Research Programme
PTSD: Post-traumatic stress disorder
POMS: Profile of Mood States
PCL-5: PTSD Checklist for DSM-5
RCT: Randomised controlled trial
SAE: Serious adverse effects
STAXI: State–Trait Anger Expression Inventory
WEMWBS: Warwick-Edinburgh Mental Wellbeing Scale
WSAS: Work and Social Adjustment Scale
SELSA-S: Short Version of the Social and Emotional Loneliness Scale for Adults
